### Statistical methods and analysis

#### Phase 1: analysis of qualitative exploration

Phase 1: To perform the process of qualitative content analysis, the audio file of each interview will be listened to attentively several times on the same day and it will be transcribed verbatim. To keep the data from the interviews confidential, a code will be assigned to each transcript. To come up with a general impression of the interviews and become fully immersed in the data, the audio files of the interviews and the transcripts will be reviewed several times, and any possible ambiguities and inconsistencies will be removed by comparing the audio files and the transcripts. The interviews will be audiotaped and a summary of the key issues in each interview will be then sent to each participant to ensure that the researcher will have accurately interpreted that participant’s comments [35]. The process of data analysis will be performed continuously and simultaneously with the data collection process. All words, sentences, and paragraphs that are related in the analysis process will be considered as a single semantic unit. After merging the semantic units, the codes will be extracted; the code together forms the subcategories and then the main categories. Finally, by abstracting the categories, they are placed in I-Change model structures. MAX.QDA software [36] will be used to manage the data.

#### Phase 5: analysis of intervention outcomes

To ensure that the data is correctly entered, a double-entry of data will be performed by two different individuals. All data obtained from women will be entered into SPSS software. A code will be defined to identify missing data. The obtained data will be kept strictly confidential and will be stored with secured and restricted access; also, the signed consent will be kept locked. Follow-up data are received using the same questionnaires as used at baseline. The intervention will be evaluated based only on Pap smear completion 3 months after the enrollment and baseline survey. Data will be summarized with descriptive statistics (mean, median, standard deviation, percentiles for numerical variables, frequencies, and percentages for categorical variables). To determine the normality of data, Smirnov and Kolmogorov will be used. Determining the frequency of demographic information in both groups is analyzed using descriptive statistics templates. To analyze the quantitative variables, the independent *t*-test and paired *t*-test are analyzed. To compare the mean score, the quantitative (intra-group) variables of the two groups of the test and control groups before and after the intervention were used as independent samples. To compare the means, the quantitative (inter-group) variables were compared between the two groups of control and test before and after paired *t*-test intervention is used. In the case of non-normalization, the mean score of the quantitative (intra-group) variables in the two groups of the test and control groups is used before and after the intervention in Mann-Whitney. To compare the meanings, the quantitative variables (inter-group) were used in both control and test groups before and after the Wilcoxon test. To determine the relationship between the underlying and dependent variables in the case of normal, the Pierson correlation test is used and the Spearman correlation test will be used to determine the relationship between the underlying and dependent variables in the case of normal. To analyze the qualitative variables, a chi-square test is used to analyze the qualitative variables. The significance level in this study is considered to be 0.5. The information obtained will be used by the related statistical software, including SPSS version 23.

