### Outcome measures

The initial research questions addressed in this study are “Does the educational intervention based on the I-Change model via mobile app affect CC preventive behaviors among Iranian women?”. To answer this main question, the following primary outcomes are expected:Determining and comparing the effects of an educational intervention designed based on the I-Change model via a mobile app knowledge related to CC prevention in women in the target and control groups before, immediately, and 3 months after the interventions.Determining and comparing the effects of an educational intervention designed based on the I-Change model via a mobile app on information factors related to CC prevention in women in the target and control groups before, immediately, and 3 months after the interventions.Determining and comparing the effects of an educational intervention designed based on the I-Change model via a mobile app motivation to CC prevention in women in the target and control groups before, immediately, and 3 months after the interventions.Determining and comparing the effects of an educational intervention designed based on the I-Change model via a mobile app predisposing factors to CC prevention in women in the target and control groups before, immediately, and 3 months after the interventions.Determining and comparing the effects of an educational intervention designed based on the I-Change model via a mobile app behavioral intention to CC prevention in women in the target and control groups before, immediately, and 3 months after the interventions.Determining and comparing the effects of an educational intervention designed based on the I-Change model via a mobile app action to prevent for CC prevention in women in the target and control groups before, immediately, and 3 months after the interventions.

Consequently, we expect the effect of our educational intervention on preventive action regarding CC among women. To assess the expected secondary outcomes, a self-reported assessment addressing preventive actions (using a condom, doing pap-test and genital examination) will be conducted.

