### Sample size and power calculations

The sample size was determined by the primary objective (comparison of participation in the experiment and control groups, respectively) and women will be allocated in equal numbers to the three randomization groups. Following the study conducted [34], the sample size we require in the quantitative phase to provide sufficient power was calculated as 61 persons for each group. This sample size was calculated to be adequate at an alpha of 0.05 and a power of .80, to test for a difference between the groups. We considered a potential dropout rate of 15%. According to the formula below, we should start with a recruitment target of 70 participants in each group: $${n}_1={n}_2=\frac{\left({s}_1^2+{s}_2^2\right){\left({z}_{1- {\propto }\!\left/ \ {2}\right.}+{z}_{1-\beta}\right)}^2\ }{{\left(\mu {\mu}_2\right)}^{2.}}$$

In line with this approach, a total of 210 women aged 18–49 years will be recruited using the inclusion and exclusion criteria listed in Table 1. Participants will be allocated into three groups (the two intervention groups plus one control group).

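### The article gives incompatible answers on which outcome decides the trial: six I-Change constructs, or Pap smear completion alone, with a sample size formula that fits only the former

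*Protocol article*

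**What the plan says.** Three sections of the protocol article bear on the deciding outcome.

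- **Outcome measures.** The list opens with "To answer this main question, the following primary outcomes are expected". It has six entries: knowledge, information factors, motivation, predisposing factors, behavioural intention and action. Each is compared at baseline, straight after the intervention and three months after it. The sixth entry reads in part "mobile app action to prevent for CC prevention in women in the target and control groups". The section then adds: "To assess the expected secondary outcomes, a self-reported assessment addressing preventive actions (using a condom, doing pap-test and genital examination) will be conducted".
- **Phase 5: analysis of intervention outcomes.** "The intervention will be evaluated based only on Pap smear completion 3 months after the enrollment and baseline survey". The same section goes on to plan t-tests, Mann-Whitney and Wilcoxon tests for score variables and chi-square tests for categorical ones.
- **Sample size and power calculations.** "The sample size was determined by the primary objective (comparison of participation in the experiment and control groups, respectively"; then "the sample size we require in the quantitative phase to provide sufficient power was calculated as 61 persons for each group". The printed formula divides a sum of two variances, times the squared normal quantiles, by a squared difference in means.

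**The concern.** The word *only* in the analysis section excludes all six constructs that the outcomes section calls primary. It also promotes one component of a secondary outcome to sole criterion. A fuller protocol or analysis plan could agree with one of these statements but not with both, so this is a conflict between positive statements and not a detail left out of an article.

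At stake is whether the trial can support a confirmatory conclusion. Both kinds of outcome will yield p-values. If a knowledge score rises and Pap uptake does not, the outcomes section supports a claim of success. If the reverse happens, the analysis section does. Participants and staff are unmasked (Randomization) and outcomes are self-reported (Limitation), so fixing the deciding outcome in advance is one of the main protections left. The choice also determines whether the stated sample size means anything for the endpoint used.

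**Working it through.** **1. The statements side by side**

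| Section | Status of the six constructs | Status of Pap testing | Time point |
|---|---|---|---|
| Outcome measures | primary | secondary (self-report), and possibly within the sixth primary, action | baseline, immediately after and 3 months after the intervention |
| Phase 5 analysis | excluded from the evaluation by *only*, yet tests for scores are planned | sole criterion | 3 months after enrolment and baseline survey |
| Sample size | not named, but the formula is for means | possibly meant by *participation* | not stated |

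No sentence orders these or gives a multiplicity rule. The time origin differs as well: one section counts from the intervention, the other from enrolment.

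**2. What the stated sample size corresponds to**

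Inputs from the sample size section: 61 per group, alpha 0.05 (two-sided, as the formula uses the 1 − alpha/2 quantile), power 0.80, dropout 15%. No mean difference or SD is printed, so 61 cannot be reproduced forward. Solved backward with equal SDs:

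d = √2 × (1.960 + 0.842) / √61 = 1.414 × 2.802 / 7.810 = 0.507, about 0.51.

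Forward check: 2 × 2.802² / 0.51² = 60.4, rounded up to 61. The recruitment figure follows as 61 × 1.15 = 70.15, about 70; dividing by 0.85 gives 72. So 61 per group is a statement about a standardised difference of roughly 0.51 on a continuous score.

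**3. What 61 per group gives if Pap completion decides**

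The formula for two proportions, with p̄ the mean of p1 and p2, is

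n = [1.960 × √(2p̄(1 − p̄)) + 0.842 × √(p1(1 − p1) + p2(1 − p2))]² / (p2 − p1)².

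The article gives no control rate for completion by 3 months. I assume the three Pap participation rates cited under Cervical cancer status in Iran.

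| Assumed control rate | Difference detectable with 80% power, n = 61 | Power for 20 points, n = 61 | n per group for 20 points | Power for 15 points, n = 61 | n per group for 15 points |
|---|---|---|---|---|---|
| 27.1% | 24.6 points | 0.63 | 91 | 0.41 | 157 |
| 50% | 24.4 points | 0.62 | 93 | 0.39 | 170 |
| 58.6% | 23.1 points | 0.67 | 84 | 0.42 | 156 |

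Worked entry: 50% against 70% has p̄ = 0.60, so n = [1.960 × √0.48 + 0.842 × √0.46]² / 0.04 = (1.358 + 0.571)² / 0.04 = 93.

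Completion within a 3-month window could be much rarer than these rates. At an assumed control rate of 5% the detectable difference is about 17 points.

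**4. Illustration of the freedom to choose**

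If k independent outcomes are each tested at 0.05 and there is no effect, the chance of at least one significant result is 1 − 0.95^k.

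- Six constructs: 1 − 0.95⁶ = 0.265.
- Six constructs plus Pap completion: 1 − 0.95⁷ = 0.302.

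The 0.05 is the level in the sample size section.

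**The case against.** The core conflict has no good defence in the text. The fair objections concern what can be built on it.

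- **Three different deciding outcomes?** A reader might infer that the sample size section names a third one. The article does not establish that. Its background uses *participation rate* for Pap testing, so the sample size section may mean the same endpoint as the analysis section. The term is ambiguous. What stands is that the formula beside it is for means.
- **Earlier Pap tests counted as completion?** A reader might infer this because follow-up reuses the baseline questionnaire. The Phase 3 section says that the questionnaire is still to be designed, so its Pap item and recall window are unknown. A baseline answer could itself identify women tested earlier.
- **The cited 27.1% to 58.6% as the share of participants already screened?** These are results of separate Iranian studies, one from a single city. They are not a population figure or a forecast for online volunteers in the north of the country. They serve above only as assumed control rates.
- **The 0.30 as the trial's error rate?** It is neither an estimate nor a bound. Constructs from one model and one questionnaire are likely to be correlated, and action overlaps with Pap testing; both lower it. The third arm and the immediate post-intervention assessment are not counted and would raise it.

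These points limit the claim but do not remove the contradiction, which depends on no figure.

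**Conclusion.** The article is wrong as written: its outcomes and analysis sections give incompatible answers on which outcome decides the trial, and preventive action appears in both outcome tiers. Until this is settled, a positive result on any one of these outcomes cannot be read as confirmatory.

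The choice changes what the trial can show. On a score, 61 per group corresponds to a standardised difference of about 0.51 (equal SDs, two-sided 0.05, power 0.80). On Pap completion, the same number reaches 80% power only for differences of about 23 to 25 points, if control rates equal the cited participation rates. A reader might therefore think that the text can be reconciled with no effect on numbers. That does not follow: if Pap completion is chosen, the sample size must be justified again, and smaller differences would need more women. The familywise figure of about 0.30 is an illustration under independence.

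**What to change.** Name one primary outcome and one time point, with its origin stated, before outcome data are seen. Make the Outcome measures, Sample size and Phase 5 analysis sections agree. Either route is coherent.

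- **If the analysis section stands:** make Pap smear completed between randomisation and month 3 the primary outcome, make the I-Change scores secondary, and restate the sample size for a binary endpoint with an explicit control rate and difference.
- **If the outcomes section stands:** delete the sentence that restricts the evaluation to Pap smear completion, choose one of the six constructs as primary (or state a multiplicity rule across them), list preventive action once, and replace *participation* in the sample size section with the chosen score.

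The cost is a protocol and registry amendment. Under the first route, the stated power may become less favourable, or the target of 70 per group may have to be revisited.

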### Participation

The research population will include women aged 18–49 years who register interested in participating in a trial intervention. Participation in the study will be stretched to all eligible women until we reach a sample size of 210 women who provide informed consent to participate.

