### Requirement

First, participants will be recruited via an online call through the virtual platforms such as Instagram pages, WhatsApp, and Telegram channel. Candidates will communicate with the trained research assistant (SK; the first author) through the phone number included in the announcement. Then, the research assistant explains the purpose of the study by phone for women who are eligible to enter the study. She will obtain contact information from potential trial participants. The assent will be sent via email or any social media messenger such as Telegram or WhatsApp. Table 1 contains a complete list of the inclusion and exclusion criteria.

**Table 1 Tab1:** Inclusion and exclusion criteria

Inclusion criteria	Exclusion criteria
Women aged 18–49 years Married (having at least one sexual relationship experience) Being the residence of North Iran during the study Tend to participate with informed consent to share information, and participate Women own a smartphone and the ability to use it Women without mental disorders, drug dependence, and addiction	Absence of more than two sessions in training sessions Having a special illness that prevents participants to take part in training sessions Woman who is not interested in the subject of the curriculum

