## Discussion

This study aims to assess the effect of the I-change model on choosing the cervical cancer prevention behaviors in Iranian women. Cervical cancer is a major public health disease in the north of Iran [37]. Even with free screening nationwide and a cervical cancer screening registry, more than 40% of eligible women do not adhere to cancer screening guidelines [37].

Many policy interventions have been performed to improve cervical cancer prevention behaviors [13, 16, 37, 38, 39, 40]; however, they were not sustained for a long time. These experiences indicate that designing appropriate interventions for promoting cervical cancer prevention behaviors and encouragement to perform a Pap smear test are necessary [41, 42, 43]. By providing the conditions, facilities, and equipment to facilitate the testing process, and paying more attention to cultural and social factors in cervical cancer and Pap smear planning, interventions, and policies, barriers to Pap testing can be eliminated [7, 44, 45, 46].

There is the widespread use of mobile technologies around the world [47], but there is currently no randomized controlled trial in Iran that describes the use of these technologies for cervical cancer screening. This study will evaluate the impact of mobile technologies on cervical cancer screening and prevention behavior practices in the north of Iran. If found to be effective in increasing adherence to screening, the mHealth intervention strategy may become an important tool for reducing the cervical cancer burden, and its associated morbidity and mortality. This could also be applied in the future for the health promotion and prevention of other major disease conditions. This requires the development of organized educational programs based on theories of behavior change.

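### Pap completion at 3 months is compared without regard to baseline screening status, so women already up to date dilute the difference between arms

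*Protocol article*

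**What the plan says.** All places are in the protocol article.

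- **Basis of evaluation.** Under Phase 5: analysis of intervention outcomes: "The intervention will be evaluated based only on Pap smear completion 3 months after the enrollment and baseline survey". The same section says: "Follow-up data are received using the same questionnaires as used at baseline".
- **Outcome hierarchy.** Outcome measures lists six I-Change constructs as primary. Pap testing comes under the secondary outcomes, where "a self-reported assessment addressing preventive actions (using a condom, doing pap-test and genital examination) will be conducted".
- **Eligibility.** Table 1 opens with "Women aged 18–49 years" and adds marriage, residence, consent, smartphone use and mental health or addiction. Its exclusions are missed sessions, special illness and lack of interest. None concerns a previous Pap test. Under Participation: "Participation in the study will be stretched to all eligible women until we reach a sample size of 210 women".
- **Allocation and analysis.** Randomization describes blocks with no stratification factor. The Phase 5 analysis names neither a subset of women due for a test nor an adjustment for earlier testing.
- **Sample size.** The sample size section gives 61 per group at alpha 0.05 and power 0.80, raised to 70 for 15% dropout. It states no Pap rates.
- **How common earlier screening is.** The section on cervical cancer status in Iran cites participation of 27.1%, 50% and 58.6%. The Discussion says "more than 40% of eligible women do not adhere to cancer screening guidelines".

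**The concern.** The app can raise Pap uptake only among women who have a test to take up. A woman tested shortly before enrolment has no test due in a 3-month window. If completion means a new test, she is a non-event in any arm, and a repeat test that was not due would score as a success. If completion means ever or currently screened, she is an event in any arm, and reusing the baseline questionnaire at follow-up leaves room for that reading. The protocol does not say which is meant.

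On both readings these women add nothing to the contrast between arms but stay in the denominator. An app that works for women who need screening could then show a small, non-significant difference. The result would also not answer the question posed in the Discussion, whether adherence to screening increases.

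**Working it through.** **1. The plan's own figure.** The 61 per group cannot be computed forward, because the printed two-means formula is given no means, SDs or rates. Solved backwards, it implies a standardised difference of (1.960 + 0.842) × √(2/61) = 0.507. The 70 matches 61 × 1.15 = 70.15. With 15% dropout, 70 × 0.85 = 59.5 per arm are analysed.

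**2. Dilution.** Let p be the rate in women due, u the share up to date, and r the rate at which up-to-date women count as completers, taken as equal in all arms. The observed rate in an arm is (1 − u)p + ur. The term ur cancels between arms, so

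observed difference = (1 − u) × (p_app − p_control).

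This holds for r = 0 (no new test), for r = 0.05 (a few repeat tests) and for r = 1 (counted as screened).

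**3. Assumptions.** The 10% (control) and 30% (app) among women due are not in the protocol. They were chosen because they give about 80% power at 59.5 per arm. The values u = 27.1% and 50% are cited participation rates. The value 60% is a ceiling, since more than 40% are said not to adhere. The value 5% is a low-share case. All figures are for one pairwise comparison at two-sided 0.05.

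**4. Power.** Power = Φ(difference/SE − 1.96), with SE = √{[p1(1 − p1) + p2(1 − p2)]/n}.

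- u = 0: SE = √(0.30/59.5) = 0.0710; 0.20/0.0710 = 2.817; power 80%.
- u = 50%, r = 0: rates 5% and 15%; SE = √(0.175/59.5) = 0.0542; 0.10/0.0542 = 1.844; power 45%.
- u = 50%, r = 1: rates 55% and 65%; SE = √(0.475/59.5) = 0.0893; 0.10/0.0893 = 1.119; power 20%.
- u = 50%, women due only: n = 29.75; SE = √(0.30/29.75) = 0.1004; 0.20/0.1004 = 1.992; power 51%.

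| u | Observed difference (points) | Power, new test (r = 5% to 0) | Power, counted as screened (r = 1) | Power, women due only |
|---|---|---|---|---|
| 0 | 20 | 80% | 80% | 80% |
| 5% | 19 | 77–78% | 70% | 78% |
| 27.1% | 14.6 | 60–63% | 37% | 67% |
| 50% | 10 | 39–45% | 20% | 51% |
| 60% | 8 | 29–37% | 15% | 43% |

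**5. Sensitivity.** A second calculation used pooled variance, 61 per group and r = 0. The effect in women due was set to give 80% power at control rates of 5%, 10% and 20%. Power was then 61–64% at u = 27.1%, 42–47% at u = 50% and 35–40% at u = 58.6%. The pattern does not depend on the 10% versus 30% choice.

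**The case against.** **Pap completion may not be the outcome that decides the trial.** This stands. The Phase 5 sentence says so, but Outcome measures makes the six constructs primary, the sample size formula is for means, and most planned tests compare mean scores. The sample size section does give some support to the Pap reading: "The sample size was determined by the primary objective (comparison of participation in the experiment and control groups, respectively". If Outcome measures governs, the point touches one component of a secondary outcome. Dilution need not affect the knowledge, motivation or intention scores.

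**The size is not documented.** This also stands. Participation rates in cited studies carry no screening interval and may mean ever tested. The same section puts participation in developing countries at 5% and says most Iranian women are unaware of the test. Volunteers may differ from all these groups.

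**A reader might infer that the trial falls short of its stated 80% power by these amounts.** The protocol does not support that. If the cited study behind the 61 also took unselected women, its effect may already be diluted. The loss is shown only against a trial of women due.

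**A reader might also infer that chance imbalance in earlier screening biases the result.** It does not. Under randomisation such imbalance is sampling variation covered by the error rate. Stratification or adjustment is worthwhile for precision.

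**Broad enrolment is legitimate in a practical trial, and analysis detail can sit in an analysis plan.** Both are fair, so restricting eligibility is not required. What the article itself fixes is a Pap outcome with no reference point for when the test was done, in a population unrestricted on screening history.

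**Conclusion.** The point holds as a defect in how the Pap outcome is defined and analysed. Under either meaning of completion, the difference between arms shrinks by the factor (1 − u), provided up-to-date women complete at the same rate in every arm. The direction is certain for any u above zero. The size is not: the loss is trivial on the new-test reading if about 5% are up to date, and large on either reading if the share resembles the cited participation rates. How much this matters for the trial's conclusion depends on whether the Phase 5 sentence or the outcome list prevails, which the protocol leaves in conflict. It is a cheap improvement worth making in either case.

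**What to change.** 1. Reconcile Outcome measures with the Phase 5 analysis section, so that the standing of Pap completion is stated once.
2. Record the date of the last Pap test at baseline and again at 3 months, and count as completion only a test dated after randomisation.
3. Where randomisation is still open, stratify the blocks by due or not due at baseline, using the screening interval the sponsor adopts. Otherwise adjust the Pap analysis for baseline Pap status.
4. Prespecify Pap completion among women due at baseline, alongside the adjusted analysis of all randomised women. The construct scores can keep all randomised women.

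The cost is one dated question at two visits, a two-level stratum and some analysis wording. The drawback is a smaller denominator: the due-women analysis restores the 20-point difference of the example but only part of the power (67%, 51% and 43% at u = 27.1%, 50% and 60%). Enrolling only women due would recover the rest. It is optional, would narrow the population, and would lengthen recruitment, an extension that the Limitation section already regards as probable.

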**Methods:**

This study involves 5 phases. In the first phase, understanding women’s perspectives will be identified using a qualitative approach based on the I-Change model. In phase 2, the results from the qualitative approach and requirement prioritization through providing experts’ perspectives will be done. The main outputs of this phase will be resulted in prioritizing the main measurable effective variables of the I-Change model. Phase 3 will be processed for the development and psychometric of an assessment tool regarding selected constructs. In phase 4, the App framework and content development will be performed. In phase 5, a three-armed, parallel-design randomized controlled trial will be conducted on women. Two hundred ten women will be randomly assigned to three groups including two intervention groups and one control group. The intervention groups included the following: (1) a mobile application and (2) a digital book. The data will be evaluated using tools designed and constructed in phase 3 of the study at baseline in 3-month follow-up assessments. The impact of the two interventions on cervical cancer prevention behaviors through mobile-based educational intervention will then be evaluated.

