### Randomization

After informed consent and baseline data collection, participants in the randomized controlled trial will be randomly assigned to the intervention and control arms in a restricted randomized block design. A research identification number will be given to each woman. Then, the identified individuals who volunteered to participate in the study were randomly assigned to the experimental and control groups using a blocking method. Following simple randomization procedures, participants will be assigned to one of the three arms of the trial in a 1:1:1 ratio according to a computer-generated randomization schedule via https://www.sealedenvelope.com/simple-randomiser/v1/lists. The letter A will be considered for the intervention group1, the letter B will be considered for the intervention group2, and the letter C for the control group. The process of random allocation will be continued continuously until the sample size will be reached. Masking of participants and study staff is not possible due to the nature of the intervention (educational) and allocation ratio.

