#### Phase 5: the randomized controlled trial for effectiveness evaluation of the app-based intervention

##### Intervention description

This study is a parallel-group randomized controlled trial. Eligible participants are randomized in a 1:1:1 allocation ratio to one of three groups: two experiment groups, in which women receive the application (app) and digital book. The training contents in both experimental groups outlined preventive behaviors of CC regarding I-Change model constructs retrieved from phases one and two. In another word, group A will be called mobile app group and group B will be called the Digi booklet-group and will receive the same training content in different ways (Fig. 1).

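### Women are randomised to app, digital book or control, but the mean comparisons are written for two groups, so the contrast that answers the app question is undefined

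*Protocol article*

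**What the plan says.** The design has three arms. The abstract states: "Two hundred ten women will be randomly assigned to three groups including two intervention groups and one control group". The Randomization section says that "participants will be assigned to one of the three arms of the trial in a 1:1:1 ratio", and the Phase 5 intervention description repeats it: "Eligible participants are randomized in a 1:1:1 allocation ratio to one of three groups". That description adds that app and digital book carry the same content, delivered differently.

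The aim (Aim, design, and outcomes) is the effect of I-Change education delivered by mobile app. The abstract promises an evaluation of both interventions.

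The analysis section (Phase 5: analysis of intervention outcomes) is written for two groups. On baseline description it says "Determining the frequency of demographic information in both groups is analyzed using descriptive statistics templates". More importantly, the sentences on mean scores also name a pair, test and control, and prescribe independent and paired t-tests, with Mann-Whitney and Wilcoxon if the data are not normal. The chi-square sentence names no number of groups. The same section sets the error level: "The significance level in this study is considered to be 0.5".

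The sample size section says "The sample size was determined by the primary objective (comparison of participation in the experiment and control groups, respectively", and gives a two-group formula for means. The requirement "was calculated as 61 persons for each group". It continues: "This sample size was calculated to be adequate at an alpha of 0.05 and a power of .80, to test for a difference between the" arms.

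**The concern.** A two-sample test cannot be applied to three arms until someone decides which women form each side. The text does not say whether app and book are combined, each compared with control, or compared with each other. The choices answer different questions:

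- Pooling tests whether either form of the material helps on average. It cannot say whether the app works.
- App against control answers the stated aim.
- App against book is the only contrast that isolates the mode of delivery, because the content is the same in both arms.

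At stake are a working app missed through dilution, a null app credited with the book's effect, or several separate tests each run at the full level. The Randomization section says that participants and staff cannot be masked, so a contrast chosen late could be chosen with results in view.

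**Working it through.** **Inputs.** Three arms at 1:1:1; 61 per group before dropout, 15% dropout, 70 recruited; alpha 0.05 and power 0.80, two-sided because the formula uses z(1−α/2) (sample size section). Six unranked primary outcomes, each measured immediately and 3 months after the intervention (Outcome measures). Significance level 0.5 (analysis section). Effect and SD are not given.

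**Step 1: what 61 represents.** With a common SD the formula is n = 2(z(1−α/2) + z(1−β))² / d². The z values sum to 1.960 + 0.842 = 2.802. Solving for d at n = 61: d = √(2 × 2.802² / 61) = 0.507. This is a back-solved assumption. It shows that 61 fits one two-group comparison at unadjusted alpha; it does not verify 61. For dropout, 61 × 1.15 = 70.15, which matches the stated 70.

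**Step 2: app and book pooled (122 against 61).** In SD units the standard error is √(1/122 + 1/61) = 0.1568.

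| True effects in the two arms | Pooled difference | Power |
|---|---|---|
| 0.507 in one, none in the other | 0.254 | Φ(1.618 − 1.960) = 37% |
| 0.507 in one, half of that in the other | 0.380 | Φ(2.427 − 1.960) = 68% |
| 0.507 in both | 0.507 | Φ(3.235 − 1.960) = 90% |

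The first row does not depend on the particular value of d. It follows from 80% power for a single pair of arms: 2.802 × ½ × √(2/1.5) = 1.618. It also cuts both ways. If only the app works, the pooled test misses it about 63% of the time. If only the book works, the test group that includes the app is declared effective about 37% of the time.

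**Step 3: arms tested separately, each at 0.05.** The independence figure is 1 − 0.95^m. The other figures come from a simulation of 200,000 draws that keeps the shared arms, with correlation between outcomes from 0.8 down to 0 and between time points of 0.5.

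| Family | Each arm vs control | All three pairs |
|---|---|---|
| One endpoint, if independent | 9.8% | 14.3% |
| One endpoint, shared arms | 9.0% | 12.3% |
| Six outcomes, one time | 24–44% | 30–54% |
| Six outcomes, two times | 39–65% | 49–76% |

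**Step 4: the printed level.** At a literal 0.5, two comparisons with control on one endpoint give 1 − 0.5² = 75% if independent, or 72% with the shared control.

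**Step 5: the endpoint.** Outcome measures lists six primary outcomes at two follow-up times and puts self-reported preventive actions, including the Pap test, under secondary outcomes. The analysis section says that evaluation rests on Pap smear completion alone, 3 months after enrolment. The error family is therefore not fixed by the text.

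**The case against.** The strongest reply is that pooling is not the only reading. The sample size section speaks of experiment and control groups, respectively, so each experimental arm may be meant to face control in its own two-sample test. The app question would then be answered, and app against book is never expressly promised as a test. The reading is plausible and lowers the error on one endpoint to about 9%. But the analysis section does not state it, and its wording, one test group and one control group, points the other way.

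A second reply is that chi-square accommodates three arms, and that if Pap smear completion is the sole endpoint, one overall test inflates nothing. That is correct. However, an overall three-arm test does not say which arm differs, and this reading contradicts the six primary outcomes.

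Three stronger claims are tempting, and the document does not support them.

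- A reader might multiply three pairs, six outcomes and two times into 36 tests and quote 1 − 0.95^36 = 84%. That needs independence, which cannot hold: the three contrasts are linearly dependent, and the scores come from the same women. The simulated range for that largest family is 49–76%, and the document does not fix that family.
- A reader might infer that power falls to 66%. That requires a Bonferroni correction over three comparisons, which nobody plans, and again the back-solved 0.507.
- A reader might treat the absence of a multiplicity rule as a defect in itself. That detail may sit in an analysis plan that is not shown. The point here rests on what the article states: two-group tests for three arms, unranked primary outcomes and conflicting levels.

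**Conclusion.** The point holds as a contradiction between design and analysis. Three arms are randomised, and the mean comparisons are specified for two. Taken literally, the plan pools app and book and does not answer its own aim; otherwise its contrasts are undefined.

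The 37% figure under pooling assumes equal arms of 61, the planned 80% power for one pair, and no effect in the second arm. It rises to 68% or 90% as the second arm's effect approaches that of the first. Under separate testing at 0.05, the supported figure is about 9% to 12% on one endpoint. Anything larger depends on how many of the six outcomes and two times are treated as confirmatory, which the article leaves open. The 0.5 level contradicts the sample size section's 0.05. Both matters should be settled before outcome data are analysed.

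**What to change.** In the Phase 5 analysis section, replace the two-group wording with arm as a three-level factor and a fixed sequence of contrasts, each at two-sided 0.05, stopping at the first non-significant step:

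1. app against control;
2. digital book against control;
3. app against digital book.

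Apply the sequence to one named primary endpoint at one time point. This requires reconciling the six primary outcomes at two follow-up times with the statement that evaluation rests on Pap smear completion at 3 months. Report all other outcomes as secondary, with confidence intervals. Correct the significance level from 0.5 to 0.05.

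For the chosen endpoint, the sequence holds the family-wise error at 0.05, because a later contrast is tested only after every earlier one has been rejected. It needs no extra women and leaves the first step at the planned power, provided that the endpoint is a mean score, as the sample size formula supposes. If Pap smear completion is chosen, 61 per group must be justified again for a proportion.

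The costs are a real decision on the endpoint, not only an edit, and later contrasts that are confirmatory only if the earlier ones succeed.
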